#### Secondary analyses

##### Cost-utility analysis

The cost-utility analysis will aim to estimate incremental cost-utility ratios (ICUR) of cost per QALY comparing the multi-faceted intervention arm and single intervention on GP arm to control arm (usual care) as follows:

ICUR = [costs _deprescribing arm_ - costs _usual care arm_] / [QALYs _deprescribing arm_ - QALYs _usual care arm_].

The costs over a one-year time horizon will be estimated from a societal perspective excluding indirect costs such as production losses as recommended by French National Guidelines on the economic evaluation of health care programs [31]. To estimate costs, the healthcare resources consumed including, PPI consumption, medical consultations, examinations, laboratory analyses and hospitalization will be valued in monetary terms using conventional tariffs of the French National Health Insurance System.

Quality of life obtained will be measured with QALYS. QALYs are a numerical composite index combining information about quality of life and survival. They are constructed by weighting each year by a quality of life factor - called a utility score - typically ranging from 0 (death) to 1 (perfect health) such that a higher score represents a more preferred health state. They will be estimated from the patient answers to the EQ-5D-5L questionnaires sent at baseline and at 1 year. The EQ-5D-5L is a generic health status questionnaire that has five dimensions (mobility, self-care, usual activities, pain/discomfort, and anxiety/depression) each of which has five levels denoting increasing problems with the dimension under consideration. The patients answers will be converted to utility scores using the French published tariffs for the EQ-5D-5L [32]. Given the time horizon of 1 year, QALYs and costs will not be discounted.

Missing data will be handled using a multiple imputation method given that considering only complete cases would not correspond to an intention-to-treat analysis [33]. The ICUR, incremental costs and QALYs will be estimated using a seemingly unrelated regression method that accounts for the correlation between costs and QALYs. The analysis will also estimate the incremental net monetary benefit criterion (the monetized version of the ICUR) to construct acceptability curves that will present the probability for an intervention to be cost-effective for various social value of the willingness-to-pay for a QALY. Finally, sensitivity analyses will be conducted to assess the robustness of the results.

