### Trial objectives

The primary objective of this study is to assess if a multi-faceted intervention is superior to single intervention and usual care to increase PPI deprescribing. Three arms will be compared: i) a multi-faceted intervention with patients using a patient education brochure and with their general practitioners (GPs) using both a personalized letter and a deprescribing algorithm ii) a single intervention on GPs and iii) no intervention (usual care).

Secondary objectives are to assess if the multi-faceted intervention has an economic efficiency compared to control group by performing a cost-utility analysis, to determine the gastroesophageal reflux disease (GERD) symptom recurrence rate, the patients’ attitudes toward deprescribing, and the characteristics of patients engaging in the deprescribing process.

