#### Secondary outcomes

Incremental cost-utility ratios: cost by quality-adjusted life-years (QALY) ratios comparing the intervention groups to control group. QALYs will be assessed from patient responses to the EuroQoL EQ-5D-5L questionnaire [25].GERD symptom recurrence using the GERD Impact Scale questionnaire [26].Patient attitude towards deprescribing using the French version of the Revised Patient Attitudes Toward Deprescribing (rPATD) [27], the *Attitude des patients envers la déprescription* (APaD) [28].Patient characteristics that succeed in deprescribing PPIs using data collected from health insurance reimbursement database.

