**Fig. 2 Fig2:**
[figure not shown]
First collection from local health insurance database 1 month before baseline and data flow. ^1^PPI DDD/year: Proton pump inhibitors defined daily dose per year; ^2^GPs: General practitioners

Healthcare resource consumption over a one-year period will be collected by combining PPI use and medical expenses related to ambulatory care (histamine-2 receptor antagonists and antacids reimbursements, consultations, technical procedures and laboratory tests). These data will be collected using the local health insurance reimbursement database (SIAM-ERASME) 12 months after baseline.

Hospital service use will be collected using the French National Health Data System (*Système National des Données de Santé*, SNDS) [29].

Measuring health-related quality of life, GERD recurrence and attitudes toward deprescribing, requires sending self-administered questionnaires with pre-paid return envelopes and to scheduling phone calls to minimize missing answers. Thus, the analysis will only be performed on a 10% sample of the population.

Thus, the EQ-5D-5L, GERD Impact Scale and rPATD questionnaires will be mailed to a 10% patient sample in each arm, 1 month before and 12 months after baseline. Patients will return the three self-reported questionnaires to the National Health Insurance by post. Phone calls will be scheduled between 8 and 10 days later to remind patients to return the three questionnaires.

The Health Insurance data managers will pair the data collected from these databases at the patient level, and proceed to data anonymization before transmission to the statistician (Fig. 3).

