### Strengths and limitations

#### Strengths

Using the PRECIS-2 tool, 6 out of the 9 domains of the multi-faceted intervention fall into the pragmatic side of the pragmatic-explanatory continuum (supplementary material 3). The pragmatic approach involves intervention at the group level rather than the individual level and as such, cluster-randomizations are the most common in pragmatic trials [35]. Also, cluster-randomization are considered as the most appropriate to conduct deprescribing trials [36].

Our trial involves a large number of patients and GPs. It is, to our knowledge, the first population-based deprescribing trial in France. We expect to exhaust the eligible population ensuring a high statistical power for a minimal difference.

By using a 3-arm design, we will be able to assess which intervention is the most effective. The single intervention on GP versus usual care will detect the effectiveness of mailing the PPI deprescribing algorithm to GP. The multi-faceted intervention will measure an additional or a combined effect of the patient education brochure.

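### The cost-utility analysis compares each intervention only with usual care, so as specified it does not show whether adding the patient brochure to the GP letter is worth its cost

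*Protocol article*

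**What the plan says.** Three places in the protocol article set the economic comparator, and all three name usual care.

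- Trial objectives: the aim is to "assess if the multi-faceted intervention has an economic efficiency compared to control group by performing a cost-utility analysis".
- Secondary outcomes: the outcome is "cost by quality-adjusted life-years (QALY) ratios comparing the intervention groups to control group".
- Cost-utility analysis: the ICUR is obtained by "comparing the multi-faceted intervention arm and single intervention on GP arm to control arm (usual care) as follows". The formula that follows subtracts usual-care costs and QALYs from those of a deprescribing arm.

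The same section and its continuation plan a seemingly unrelated regression for incremental costs and QALYs, an incremental net monetary benefit, and acceptability curves. None of these is tied to a multi-faceted versus single contrast.

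On costs, the section states that "the healthcare resources consumed including, PPI consumption, medical consultations, examinations, laboratory analyses and hospitalization will be valued in monetary terms". Unit prices are to come from the national insurer's standard tariffs. The Data collection procedures section describes resource use as "combining PPI use and medical expenses related to ambulatory care (histamine-2 receptor antagonists and antacids reimbursements, consultations, technical procedures and laboratory tests", with hospital use taken from the national health data system.

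**The concern.** The Interventions section makes the multi-faceted arm the single arm plus a patient brochure. A payer choosing among usual care, letter alone, and letter with brochure can adopt only one. The brochure therefore has to be judged on what it adds in cost and QALYs over the letter. Against usual care, the brochure is credited with whatever the letter achieves.

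The rest of the plan sees this. The primary outcome, the GERD scores and the attitude scores are all to be compared across all arms. The Strengths section says the multi-faceted arm is there to measure what the brochure adds or does in combination. The economic analysis alone fixes its between-arm comparisons to control.

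The Conclusion envisages wider, national use of the multi-faceted strategy if it proves effective. A favourable ratio against usual care would be a natural argument for that, even if the letter produced most of the benefit.

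**Working it through.** The documents state no ICUR, unit cost or QALY value, so there is no planned figure to reproduce. The check is whether the two planned ratios answer the brochure question. **All costs and QALYs below are assumed.**

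**Formulas.** Write C and E for incremental cost and QALYs against usual care, with M for multi-faceted and S for single.

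- Planned: R_M = C_M / E_M and R_S = C_S / E_S.
- Needed for the brochure: R_MS = (C_M − C_S) / (E_M − E_S).

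**Illustration 1.** Take S at +2 euros and +0.0010 QALY, and M at +14 euros and +0.0014 QALY.

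- R_S = 2 / 0.0010 = 2,000 per QALY
- R_M = 14 / 0.0014 = 10,000 per QALY
- R_MS = (14 − 2) / (0.0014 − 0.0010) = 12 / 0.0004 = 30,000 per QALY

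Here the letter gives 0.0010 / 0.0014 = 71% of the QALY gain for 2 / 14 = 14% of the added cost. The increment for the brochure is three times the ratio the plan would report.

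**The two planned ratios do not fix the third.** Let r = E_S / E_M. Substituting C = R × E gives R_MS = (R_M − r × R_S) / (1 − r). Hold both planned ratios at 2,000 and 10,000 and vary only r:

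- r = 0.5: (10,000 − 1,000) / 0.5 = 18,000
- r = 0.714: (10,000 − 1,429) / 0.286 = 30,000 (rounded)
- r = 0.8: (10,000 − 1,600) / 0.2 = 42,000

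**Illustration 2.** Take S at +20 and +0.0020 QALY (R_S = 10,000), hold M at +50, and vary the QALY gain of M:

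| E_M | R_M = 50 / E_M | R_MS = 30 / (E_M − 0.0020) |
|---|---|---|
| 0.0040 | 12,500 | 15,000 |
| 0.0025 | 20,000 | 60,000 |
| 0.0022 | 22,727 | 150,000 |
| 0.0019 | 26,316 | dominated by S |

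The gap ranges from small (12,500 against 15,000) to a reversal of the decision.

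**Likely precision.** A 10% sample of 33,000 is 3,300 patients, or 1,100 per arm before non-response. Assume a QALY SD of 0.1 to 0.3 and 1,100 down to 550 respondents per arm, ignoring clustering and baseline adjustment. Then SE = SD × √(2/n):

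- lowest: 0.1 × √(2/1,100) = 0.0043
- highest: 0.3 × √(2/550) = 0.0181

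At an assumed 30,000 per QALY this is about 130 to 540 euros. The 0.0004 QALY increment of illustration 1 is 11 to 45 times smaller than these SEs.

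**The case against.** The strongest reply has four parts.

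**The contrast is obtainable.** If one regression covers the three arms, multi-faceted versus single is a linear contrast of quantities already estimated. If incremental costs and QALYs are printed separately, a reader can subtract the point estimates. This stands. A reader might infer that the trial cannot answer the brochure question, and the documents do not support that. What is missing is any plan to report the contrast. Its uncertainty also needs the covariance of the two estimates, which a reader would not have.

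**There is no contradiction.** The economic objective names control as comparator, and the analysis follows it. The statement "By using a 3-arm design, we will be able to assess which intervention is the most effective" concerns deprescribing effectiveness, which the primary analysis covers by comparing all arms. This also stands. The point is a poor choice of comparator, not an inconsistency.

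**Mailing costs may well be counted.** A reader might infer that printing and postage are left out of the numerator. The listed items are care consumed, valued at insurance tariffs, and delivery costs do not fit there naturally. But the list opens with a word that leaves it unclosed, the perspective is societal, and this is a condensed article. The omission is not established. Nor do the documents show that mailing is the main cost difference between the active arms, or that the single arm will have the lower total cost. The trial itself will measure total cost.

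**Sampling error will dominate.** On the assumptions above it would swamp both a few euros of postage and a very small QALY increment. That limits how decisive the added contrast can be. It does not justify omitting it, since net monetary benefit and acceptability curves exist to express such uncertainty.

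**Conclusion.** The point holds as a weakness in a stated analysis rule. The plan fixes usual care as the only economic comparator for both interventions, so the ratios it will report do not show whether the brochure is worth adding to the letter. A favourable multi-faceted ratio could come mostly from the letter.

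The size cannot be read from the documents. Under assumed inputs the brochure's own ratio runs from slightly above the reported one, through three times as high, to dominated. The structural conclusion does not depend on those inputs. It follows from the multi-faceted arm containing the single arm's materials and from two ratios not determining a third.

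This is worth correcting because it bears on adoption, but it affects a secondary analysis only. The delivery-cost question is a minor clarification.

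**What to change.** Amend the cost-utility analysis in the protocol or SAP before the economic data are analysed:

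1. Fit the planned seemingly unrelated regression jointly to the three arms.
2. Report a full incremental analysis: order the strategies by estimated total cost, remove dominated ones, and give each remaining ICUR against the next less costly strategy.
3. Report multi-faceted versus single incremental costs, QALYs and net monetary benefit with their uncertainty, whatever the ordering turns out to be.
4. Draw acceptability curves with all three strategies competing.
5. State whether producing and mailing the brochure and letters is costed in each active arm, and from what source.

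The ratios against usual care can stay. The cost is a few lines of text, one more contrast from the same model, and unit costs for delivery if they are not already included. No further patient data are needed. The drawback is an incremental estimate that will probably be imprecise in the questionnaire sample, and the report should say so.

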### Outcome measures

#### Primary outcome

PPI deprescribing will be defined as the proportion of patients achieving a 50% decrease in their PPI reimbursement (Defined Daily Dose (DDD)/year) at the end of the intervention (at 12 months compared to baseline).

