#### Limitations

Despite these strengths, our trial has several limitations. Firstly, regarding the deprescribing rate and the cost-utility analysis, our data will be collected from the health insurance reimbursement database. This database only estimates the consumption of medications through their reimbursements [37]. PPI consumption can be overestimated because real patient intake depends on adherence. Conversely, this database does not compile over-the-counter PPI but they are less used than reimbursable PPI [38].

Secondly, the secondary outcome on GERD recurrence is assessed by the GERD impact scale questionnaire at 12 months after baseline. Thus, we may miss GERD recurrence caused by an early acid rebound due to PPI withdrawal. However, sending this questionnaire during the intervention may influence patients’ perceptions, resulting in a participation bias on the primary outcome. We chose to keep our trial without further interventions during the study period. The GERD impact scale will only assess the GERD recurrence following PPI deprescribing.

Thirdly, neither patients nor their GP will be blinded because of the pragmatic trial design [39]. However, the participants will not be informed of the different interventions occurring during the year of the trial. Data managers and statisticians will be blinded to the allocation arm. Primary outcome (PPI deprescribing) is objective and not subject to interpretation.

Fourthly, because of logistical constraints, only a 10% sample of the population (nearly 3300 patients) will have the opportunity to answer questionnaires on secondary outcomes. The questionnaires will be sent by mail and the number of participants will depend on response-rate. However, the response-rate should be increased due to pre-paid return envelopes and amplified by phone reminders, as reported by Neve et al. for patient reported outcomes [40].

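### The cost-utility analysis is labelled societal, but the described data cover reimbursed care only, so switching to non-reimbursed acid suppressants would appear as a full saving

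*Protocol article*

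**What the plan says.** The Cost-utility analysis section of the protocol article states that costs over one year "will be estimated from a societal perspective excluding indirect costs such as production losses", citing French national guidelines. The resources consumed "will be valued in monetary terms using conventional tariffs of the French National Health Insurance System".

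Data collection procedures gives the sources. Healthcare consumption combines PPI use with "medical expenses related to ambulatory care (histamine-2 receptor antagonists and antacids reimbursements, consultations, technical procedures and laboratory tests"), and "These data will be collected using the local health insurance reimbursement database (SIAM-ERASME) 12 months after baseline". For inpatient care, "Hospital service use will be collected using the French National Health Data System". No other source of cost data is described.

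The Limitations section says that the deprescribing rate and the cost-utility analysis both rest on the reimbursement database. It adds that "this database does not compile over-the-counter PPI but they are less used than reimbursable PPI". The primary outcome is "the proportion of patients achieving a 50% decrease in their PPI reimbursement". The cost-utility plan also promises net-benefit acceptability curves and sensitivity analyses, without naming any.

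**The concern.** A societal perspective that removes only indirect costs keeps patients' direct spending on medicines. The described data contain none of the non-reimbursed part of it. The label therefore promises more than the data can deliver.

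The gap lies where this intervention acts. A patient whose reimbursed PPI is cut and who then buys a PPI, an H2 antagonist or an antacid without reimbursement shows the whole reimbursed amount as a saving. For the insurer that saving is real. Under the stated perspective it is partly a transfer to the patient. The plan itself takes symptom return seriously: GERD recurrence is a secondary outcome, and reimbursed H2 antagonists and antacids are costed. Reimbursed substitution is thus counted and purchased substitution is not.

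The reason given for setting the gap aside concerns how common over-the-counter PPI is overall. It says nothing about switching after a cut, or about whether switching differs by arm. At stake is whether the ICUR, net benefit and acceptability curves can be read as societal results when the conclusion looks towards national implementation.

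**Working it through.** **Perspective against data**

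| Element | Stated scope or source | Non-reimbursed purchases included? |
|---|---|---|
| Perspective | Societal, minus indirect costs | Yes, by implication |
| PPI, H2 antagonists, antacids | Reimbursement database | No |
| Consultations, procedures, tests | Reimbursement database | No |
| Hospital use | National health data system | Not applicable |
| Valuation | National Health Insurance tariffs | No |

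The plan states no figure for switching or its cost, so there is none to reproduce. What follows is a range.

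**Inputs.** Deprescribing rates p1 (intervention) and p0 (control) are from Table 1 under Sample size and power: 17% or 10% against 7% or 2%. s1 and s0 are the shares of deprescribed patients who replace reimbursed PPI with a non-reimbursed product. O is a switcher's average annual out-of-pocket spending. s and O are assumptions; the documents give neither.

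**Cost.** The incremental cost recorded per patient omits

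(s1·p1 − s0·p0) × O.

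The recorded saving, and the net benefit, are too favourable to the intervention by this amount whenever s1·p1 exceeds s0·p0, that is, whenever s1/s0 > p0/p1. At 17% vs 7% the threshold is 7/17 = 0.41; at 10% vs 7% it is 7/10 = 0.70. An equal switching share gives a ratio of 1 and lies above both.

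**Where switchers fall if s is equal.** The intervention arm's share within a pair is p1/(p1 + p0): 17/24 = 71%, 10/17 = 59%, 17/19 = 89%, 10/12 = 83%.

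**Deprescribing difference without switchers.** p1(1 − s1) − p0(1 − s0), assuming that each switcher fully replaces the PPI.

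| Rates | s1, s0 (assumed) | Omitted cost per patient | Difference without switchers |
|---|---|---|---|
| 17% vs 7% | 10%, 10% | (0.017 − 0.007)·O = 0.010·O | 15.3 − 6.3 = 9.0 points |
| 17% vs 7% | 30%, 30% | (0.051 − 0.021)·O = 0.030·O | 11.9 − 4.9 = 7.0 points |
| 17% vs 7% | 20%, 10% | (0.034 − 0.007)·O = 0.027·O | 13.6 − 6.3 = 7.3 points |
| 10% vs 7% | 10%, 10% | (0.010 − 0.007)·O = 0.003·O | 9.0 − 6.3 = 2.7 points |
| 10% vs 7% | 30%, 30% | (0.030 − 0.021)·O = 0.009·O | 7.0 − 4.9 = 2.1 points |

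The observed differences are 10 points (first three rows) and 3 points (last two). The monetary size of the omitted cost cannot be stated without O. The cost formula counts only patients who reach the 50% cut; purchases after smaller cuts would come on top.

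**Tipping point.** With the recorded incremental net benefit B per patient, the conclusion changes when (s1·p1 − s0·p0) × O = B. Every term except s and O will be known at analysis.

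**The case against.** Much of the defence is sound. The over-the-counter gap is disclosed, expressly for both endpoints. The perspective is qualified by reference to national guidelines that are not at hand, so whether they require non-reimbursed purchases cannot be checked. The cost list need not be exhaustive, and tariffs may include the patient's share of reimbursed items. What is clearly missing therefore narrows to non-reimbursed purchases. The switching shares are assumed, and even the unequal scenario leaves 7.3 points, while Table 1 gives power above 0.90 for a 3-point difference.

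A reader might infer more than the documents support:

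- *That the primary outcome is misclassified.* It is defined as a fall in reimbursement, and a switcher whose reimbursed PPI halves meets that definition.
- *That the claim "Primary outcome (PPI deprescribing) is objective and not subject to interpretation" is contradicted.* In context it answers the lack of blinding. It concerns assessment, not completeness of PPI capture.
- *That the trial asks patients nothing about purchased products.* The items of the mailed questionnaires are not reproduced, so this cannot be known. No use of them to cost such products is described.
- *That switching is known to be concentrated in the intervention arms.* This follows from the hypothesised rates only if switching shares are not much lower there.

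Disclosing the gap does not settle the label. The Limitations section neither connects the gap to the societal perspective nor considers a difference between arms, and relative overall use does not answer either point.

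**Conclusion.** The stated perspective and the described data do not match: the analysis can support conclusions about reimbursed care, not societal ones. The gap favours the intervention in the cost results if switching shares are similar across arms or higher with intervention. At 17% vs 7%, with s assumed at 10-30% in both arms, the omitted cost is 0.010 to 0.030 of a switcher's annual spending per patient. Neither s nor that spending is given, so whether the cost-utility conclusion would change is unknown.

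The deprescribing result stands as a result about reimbursement. It should not be read as an equal fall in total PPI exposure; under the same assumptions, 10 points would correspond to 9 to 7, or to 7.3 with s of 20% vs 10%. This does not show a biased primary analysis.

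**What to change.** 1. In the Cost-utility analysis section, restate the perspective as that of reimbursed health care valued at National Health Insurance tariffs. Limit the ICUR, net-benefit and acceptability-curve conclusions to it.
2. Among the sensitivity analyses already promised there, name one that varies an arm-specific s, adds an assumed out-of-pocket cost per switcher, and reports the s at which the cost-utility conclusion changes. Show the deprescribing difference over the same range.
3. State with the primary outcome that it measures reimbursed PPI, not total exposure.

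The cost is a narrower claim and a little extra analysis, with no new data. A new questionnaire item is not proposed. Under Timeframe the mailings were scheduled for mid-October 2020 and mid-November 2021, before publication in February 2022, and the questionnaires' content is not shown. Trial status describes data collection as still under way until the end of 2022.

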## Methods

### Study design and setting

The trial is designed as a prospective, open-label, cluster-randomized parallel-controlled study within a 12-month period. The unit of randomization will be the GPs practice. This pragmatic population-based trial will be conducted in every eligible GP practice in two regions of Western France (Loire-Atlantique and Vendée).

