### Recruitment and allocation

Each GP practice and its associated patients will be defined as an individual cluster to avoid contamination bias between GPs and/or between patients [21]. These clusters will be randomized in three arms using a 1:1:1 ratio. Eligible patients will be identified using the local health insurance reimbursement database.

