### Sample size and power

Preliminary analyses showed that around 33,000 patients, 1300 GPs and 684 practices would meet inclusion criteria in 2017, which corresponds to a mean of 1.9 GPs and 48.3 patients per practice. Using an intraclass correlation coefficient (ICC) of 0.05 thus lead to an inflation factor of 3.365. Literature data suggested a “natural” PPI deprescribing rate between 2 and 7% in the control arm [17, 20, 30].

Assuming an inflation factor of 3.365 and using a two- sided alpha of 0.05, we will have 90% power to detect a minimum true difference of 9.5% of PPI deprescribing rates between the multi-faceted intervention arm and the control arm. These estimates change slightly if different natural deprescribing rates and higher ICCs are assumed (Table 1).

**Table 1 Tab1:** Sample size simulation

“Natural” PPI deprescribing rate	PPI deprescribing rate due to intervention	Patients per cluster	Intracluster Correlation Coefficient	Power
2%	17%	45	0.05	> 0.999
2%	17%	50	0.05	> 0.999
2%	17%	45	0.1	> 0.999
2%	17%	50	0.1	> 0.999
2%	10%	45	0.05	> 0.999
2%	10%	50	0.05	> 0.999
2%	10%	45	0.1	> 0.999
2%	10%	50	0.1	> 0.999
7%	17%	45	0.05	> 0.999
7%	17%	50	0.05	> 0.999
7%	17%	45	0.1	> 0.999
7%	17%	50	0.1	> 0.999
7%	10%	45	0.05	> 0.994
7%	10%	50	0.05	> 0.990
7%	10%	45	0.1	> 0.930
7%	10%	50	0.1	> 0.908

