#### Primary analysis

PPI deprescribing rate at 12 months will be compared between each arm using a generalized linear mixed model. This model accounts for the random effect of GP practice.

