##### Patient attitudes toward deprescribing

Cross-tabulations between the different rPATD questions and patient characteristics, and successful deprescribing at 12 months will be performed using Cochran-Armitage tests. Patient attitude measured from Likert scale will be compared between each arm with a generalized linear mixed model to account for the random effect of GP’s practice.

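### The cost-utility comparison of arms, as written, allows for the correlation between costs and QALYs but not for randomization by GP practice, so its uncertainty would be somewhat understated

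*Protocol article*

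**What the plan says.** The design is clustered throughout. Study design and setting states: "The unit of randomization will be the GPs practice". Recruitment and allocation adds: "Each GP practice and its associated patients will be defined as an individual cluster", and "These clusters will be randomized in three arms using a 1:1:1 ratio". Sample size and power applies an inflation factor for clustering.

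The analysis sections mostly follow the design. Of the primary model the article says: "This model accounts for the random effect of GP practice". The GERD score comparison, the between-arm attitude comparison and the model for characteristics of successful patients each name the same random effect.

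The Cost-utility analysis section compares each intervention arm with usual care and specifies: "The ICUR, incremental costs and QALYs will be estimated using a seemingly unrelated regression method that accounts for the correlation between costs and QALYs". Net monetary benefit and acceptability curves come from this analysis. Missing data are to be multiply imputed, and sensitivity analyses are announced without detail. The section mentions no practice effect, clustered standard error or cluster bootstrap, and does not bring practice into the imputation.

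**The concern.** The correlation that the section handles lies within a patient, between that patient's cost and QALY. Randomization by practice creates a different one, between patients who share a practice and therefore an arm. Handling the first does nothing for the second. If both equations contain the same regressors, seemingly unrelated regression gives the same point estimates as ordinary least squares in each equation, and its usual standard errors assume independent patients.

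With a positive ICC the error has one direction: intervals for incremental cost, QALYs and net benefit are too narrow, and the acceptability curve is too extreme. The point estimates are not the issue. The economic result is the only between-arm model in the article without a practice term, so its precision would not be on the same footing as the rest.

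**Working it through.** **Inputs from the article.** Sample size and power: "around 33,000 patients, 1300 GPs and 684 practices would meet inclusion criteria in 2017". The same section gives an average practice size of 48.3 patients, an ICC of 0.05 for deprescribing, an inflation factor of 3.365, and 0.10 as the higher ICC in Table 1. Data collection procedures and Limitations: questionnaires go to a 10% sample, nearly 3,300 patients. Allocation 1:1:1 gives 684/3 = 228 practices per arm.

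**Assumptions.** The article gives no ICC for costs, QALYs or net benefit. I use 0.01, 0.05 and 0.10; the last two are the values it uses for deprescribing. I also assume that the 10% sample is spread evenly over practices, since the article does not say how it is drawn.

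**Step 1: reproduce the plan's own figure.** Design effect DE = 1 + (m − 1) × ICC, with m patients per practice. 1 + (48.3 − 1) × 0.05 = 3.365, as printed.

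**Step 2: cluster size in the questionnaire sample.** 48.3 × 0.10 = 4.83 patients per practice if everyone responds.

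**Step 3: consequences of leaving out clustering.**
- True SE / naive SE = √DE.
- Actual type I error of a nominal two-sided 5% test = 2 × [1 − Φ(1.96/√DE)].
- An acceptability probability reported as 0.95 (z = 1.645) should be Φ(1.645/√DE).

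| Patients analysed | m | ICC | DE | √DE | Type I error | 0.95 becomes |
|---|---|---|---|---|---|---|
| 10% sample, full response | 4.83 | 0.01 | 1.04 | 1.02 | 5.4% | 0.947 |
| | | 0.05 | 1.19 | 1.09 | 7.3% | 0.934 |
| | | 0.10 | 1.38 | 1.18 | 9.6% | 0.919 |
| 10% sample, 50% response (assumed) | 2.415 | 0.01 | 1.01 | 1.01 | 5.2% | 0.949 |
| | | 0.05 | 1.07 | 1.03 | 5.8% | 0.944 |
| | | 0.10 | 1.14 | 1.07 | 6.7% | 0.938 |
| All patients (not stated in the article) | 48.3 | 0.01 | 1.47 | 1.21 | 10.6% | 0.912 |
| | | 0.05 | 3.365 | 1.83 | 28.5% | 0.815 |
| | | 0.10 | 5.73 | 2.39 | 41.3% | 0.754 |

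Example, second row: DE = 1 + 3.83 × 0.05 = 1.19; √DE = 1.092; 1.96/1.092 = 1.795; type I error = 2 × [1 − Φ(1.795)] = 7.3%.

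**Step 4: check by simulation.** Two arms of 228 practices, no true difference, arm as the only regressor, 2,000 runs per setting. With an average of 4.83 patients per practice and ICC 0.01 / 0.05 / 0.10, the naive test rejected in 5.2% / 7.8% / 10.8% of runs, and the cluster-robust test in 4.9% / 5.2% / 4.7%. With 48 patients per practice and ICC 0.05 the rates were 30.1% and 5.8%. This agrees with the formulas, and clustered standard errors bring the error rate back to about 5%.

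**The case against.** The strongest reply is that the article is silent on clustering here and does not rule it out. It names an estimator for the coefficients but not how standard errors or acceptability curves are computed, and practice-clustered errors or a practice bootstrap would fit within its sentence. A condensed article may leave that to a health-economic plan. This stands in part: the point concerns the method as written, and an unseen plan may already settle it. But the section does say which dependence its method handles, and the neighbouring analyses state the practice effect in a single clause, so lack of space hardly explains the difference.

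The second reply is that the effect is small, and it largely stands. In the 10% sample the distortion is modest, non-response shrinks it further, and the ICC is an assumption.

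A reader might infer three stronger points that the article does not support:

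- **A type I error near 29%.** This needs the economic analysis to run on all 33,000 patients at ICC 0.05. The article nowhere says so, and it limits the quality-of-life analysis to the 10% sample.
- **The same defect in the attitude cross-tabulations.** The article says that cross-tabulations of questionnaire answers and patient characteristics with "successful deprescribing at 12 months will be performed using Cochran-Armitage tests". These do not compare randomized arms. With m = 4.83 and ICCs of 0.05 to 0.10 for both the answer and success, the variance inflation is about 1 + 3.83 × ICC × ICC, which is 1.01 to 1.04. The between-arm comparison of attitudes already has a practice effect.
- **A threat to the case for national roll-out.** The Conclusion ties wider implementation to demonstrated effectiveness and does not mention cost-utility. The effectiveness model includes the practice effect.

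**Conclusion.** The point holds with moderate severity. As written, the between-arm cost-utility analysis leaves out the clustering by which the trial is randomized, and its intervals and acceptability curves would be somewhat too confident. In the 10% sample with full response, and for an assumed ICC of 0.01 to 0.10, the true standard error is 1.02 to 1.18 times the naive one. The size rests on that assumed ICC, on even sampling across practices, and on the usual independence standard errors being used. If the sample were instead concentrated in fewer practices, m and the design effect would rise. The outcome is secondary, and the primary comparison is not affected.

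**What to change.** State in the analysis plan that uncertainty in the cost-utility analysis will reflect randomization by practice. Any of three routes would do:

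- keep the seemingly unrelated regression and use practice-clustered standard errors, which is the smallest change and is well supported by about 228 practices per arm;
- fit a bivariate mixed model for costs and QALYs with practice random intercepts;
- use a two-stage bootstrap that resamples practices and then patients within them.

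Account for practice in the multiple imputation as well, because an imputation model that ignores it dilutes the within-practice correlation in the completed data. Derive the net-benefit intervals and acceptability curves from the same fit. State which patients enter the cost and QALY equations and how the 10% sample is spread over practices, since these fix the size of the effect.

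The cost is a few sentences in the plan and a few lines of code, with no new data. Intervals become about 2% to 18% wider in the 10% sample under the assumed ICCs, and less so with non-response.
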